#### Validity and reliability of the ACP Engagement Survey

In a prior study, we established the validity and reliability of the ACP engagement survey in 50 older adults, aged 60 years or older with two or more chronic or serious illnesses (32 % female, 42 % non-white). Internal consistency of the survey was high with a Cronbach’s alpha of 0.94 for Process Measures. Seven-day test-retest reliability was also high with interclass correlations of 0.70 for Process Measures and 0.87 for Action Measures. We also tested discriminant validity by comparing process and action scores for older adults to healthy young adults and found statistically significant differences [22]. Furthermore, this survey has been used in pilot testing and has been shown to be able to detect ACP behavior change in response to the PREPARE website [15].

#### Measures related to engagement and satisfaction in decision-making

Engagement in decision-making is measured with two items (Table 2, desired role in decision-making). Satisfaction with decision-making is assessed with the Decisional Conflict scale for those who report a decision was made [31]. The Decisional Conflict scale consists of three subscales assessing decisional uncertainty, factors contributing to uncertainty, and decisional effectiveness.

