Although the easy-to-read advance directive was shown to be an improvement over standard forms, through additional formative work, we found that most patients go through a series of ACP behavioral steps that extend beyond simply filling out an advance directive. For example, 6 months after exposure to the easy-to-read advance directive, only 13 % completed an advance directive whereas 61 % of older adults contemplated ACP, 56 % discussed ACP with family or friends and 22 % discussed ACP with clinicians [14]. These data support the need to engage patients in a full range of ACP activities in addition to having them complete legal advance directive forms.

Based on our prior work [15] and the work of others [16, 17], we developed and published an updated paradigm of comprehensive ACP that shifts the focus from completion of advance directives to preparing patients to communicate their goals of care with surrogates and to actively participate with clinicians in making the best possible in-the-moment decisions [11]. To operationalize this new paradigm, we created an easy-to-read, culturally-appropriate website called PREPARE (www.prepareforyourcare.org). PREPARE is targeted to a 5^th^- grade reading level and was designed to be completed outside of a clinical setting without supervision or facilitation. PREPARE includes communication training on how to 1) choose and ask a surrogate; 2) clarify and communicate one’s values; 3) discuss leeway in surrogate’s decisions (allow surrogates to use their best judgment); 4) inform clinicians, family, and friends of one’s decisions; and 5) ask clinicians appropriate questions to make informed medical choices [11]. Extensive videos are used to demonstrate, through modeling, how to make ACP decisions and to communicate with surrogates and clinicians [15, 18–20]. Our pilot findings showed that, among diverse older adults, PREPARE significantly improved engagement and behavior change in ACP. Furthermore, it was rated a 9 out of 10 for ease of use, despite limited health literacy and lack of computer experience in this cohort of older adults [15].

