The goal of this randomized controlled trial is to determine the efficacy of PREPARE to engage Veterans in the full comprehensive process of ACP. Consistent with prior studies in the field, our primary outcome is advance directive completion. In addition, important secondary outcomes include identifying goals for medical care, communicating with surrogates and clinicians, and making informed medical decisions.

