### Aims and primary hypotheses

The primary hypothesis of this study is that older Veterans randomized to the PREPARE arm (the PREPARE website plus the easy-to-read advance directive), compared to the control arm (the easy-to-read advance directive alone), will have increased rates of ACP documentation in their medical record (advance directives, clinicians notes, code status orders). Because this is the standard outcome measure for advance care planning, it is the outcome on which we calculated our sample size (see Sample Size Section). However, ACP consists of several behavioral processes (knowledge, contemplation, self-efficacy, and readiness) for several discrete ACP behaviors, including identifying surrogates, identifying values, and communicating this information with clinicians, surrogates, and other loved ones. Therefore, we feel our secondary outcomes and hypotheses are just as clinically meaningful. The secondary hypotheses of this study are that older Veterans randomized to the PREPARE arm, compared to the control arm, will have greater engagement in ACP including behavior change process measures and additional ACP actions beyond advance directive documentation as measured by a validated survey [22]. Secondary hypotheses also include greater Veteran activation and clinician responsiveness within the clinical encounter as measured by audio-recording a subset of clinical visits, Veteran satisfaction with clinician communication, Veteran engagement and satisfaction with decision-making, surrogate-reports of Veteran engagement in ACP behaviors, and fewer reported barriers to ACP for the PREPARE versus control arm. Other outcomes include comparisons of acceptability and usability of the PREPARE website plus an easy-to-read advance directive versus an advance directive alone (Table 2).

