	Secondary outcome variables							
Communication quality	Modified CAHPS (that is, did this provider explain things in a way that was easy to understand?)	14	Comparative Fit Index = 0.98, Tucker Lewis Index = 0.98		X	X		
			Internal consistency: 0.58 to 0.92. ≥ 0.70 for four of eight constructs [62]					
Satisfaction with communication	For example, “How satisfied are you that you could share your most important concerns with X/that X understood what was most important to you?)	8			X	X	X	X
Satisfaction with care	Care Consistent with Goals: Comparison of 10-point ratings about aggressiveness of care desired and care currently receiving.	4			X			X
Barriers to ACP	Checkbox of 13 common barriers (for example, thinking about the topic makes me nervous or sad; I am too healthy; I am too busy; my family or doctor is too busy; I prefer to leave my health in God’s hands; I don’t want to burden my family and friends; I want to leave the choice to my friends and family; I want to leave the choice to my doctors; and an open-category response for “other.”)	13	Associated with ACP [25]		X			X
Attitudes about ACP	Processes of change for ACP [16]	34	Responsive to ACP intervention [15]		X			
Desired role in decision-making	Control Preference Scale (CPS) [58]	2	Correlation between preferred and actual role in decision-making [59–61]		X			X
Satisfaction with decision making	Decisional Conflict Scale	20	test-retest coefficient = 0.81			X	X	X
			α coefficient: 0.78-0.92 for total scale. 0.58-0.92 for subscales [31]					
Depression and anxiety	Patient Health Questionnaire (PHQ-4)	4	Cronbach’s α = 0.78 [63]		X	X	X	X
Surrogate reports of patient engagement in ACP and other surrogate items	Modified from the ACP Engagement Survey [22], (for example, “Did [Veteran] ask you to be their surrogate decision maker, talk to you about leeway, talk to you about their values, tell other family or friends about their wishes, ask clinicians questions or have you ask clinicians questions?”	45						X
	Prior ACP	6						
	Care consistent with goals	4						
	Decisional Conflict	19						
	Implementation	13						
Implementation: acceptability	Acceptability and Usability		1 factor explained 81-85 % of variance/scale. Kuder-Richardson >0.75 [12]		X			
	(a) Ease of use and understanding	8						
	(b) Usefulness in decisions & discussions	6						
	(c) Attitudes about norms or expectations	6						

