#### Measures related to Veteran activation within primary care encounters

Veteran activation within the clinical encounter is assessed by audio-recording primary care visits using [name] communication coding system. This system defines activation as the degree to which patients ask questions, express concerns, offer opinions, state preferences, introduce new topics, or make decisions [33]. These behaviors are considered active because they have been shown to influence clinician’s behavior and treatment decisions [19]. We are interested both in activation in general throughout the consultation and in any discussions of ACP [34]. Therefore, we will assess overall activation and ACP-specific activation. The number of activation utterances will be assessed by independent, blinded coders and will be included in a composite measure. Utterances will also be coded as “self-initiated” or “prompted”, depending on whether the activation was solicited or encouraged by the physician. An increase of one patient activation utterance is considered clinically relevant. The codes of patient activation will be transformed into quantitative data and stored in a relational database that can be exported for quantitative analysis. To protect against rater drift and decay, continuous monitoring of inter-rater reliability will occur throughout the entire coding period by double-coding 20 % of the conversations. The coders will resolve any coding disagreements by conference; the entire team will resolve persistent disagreements.

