## Outcomes and Sample Size Calculations

### Primary outcome

The primary outcome is advance directive documentation in the medical record. This outcome was selected based on prior studies that have shown that advance directive interventions can increase documentation. A meta-analysis demonstrated a pooled effect size of 0.50 (95 % CI; 0.17-0.83) suggesting a positive effect associated with advance directive interventions [36]. One RCT of an ACP workbook in older Veterans also demonstrated an increase in living wills documented from 23 % in controls to 48 % in the intervention group (*P* < .001); and ACP notes from 24 % to 47 % (*P* < .001) [37]. Consistent with results from prior studies, our pilot study showed that a literacy appropriate advance directive doubled completion rates from baseline [12]. From SFVAMC administrative data, 11 % of the potential study sample had an advance directive in their medical record. We assume that after being included in the study, the control group may have an advance directive documentation rate of 15 %. If we assume doubling of the percent of ACP discussion notes between groups (what we consider clinically significant), a sample size of 350, or 175 in each arm, will afford us 92 % power with a two-tailed alpha of 0.05 to detect an elevation in rate of advance directive documentation from 15 % in controls to 30 % in the PREPARE group and 80 % power to detect a difference of 15 % in controls versus 27 % in the PREPARE group. After accounting for an estimated 15 % attrition rate, including death at 6 months (based on prior work) [12], our recruitment target is 410 Veterans or 205 in each arm.

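### Satisfaction with decision-making is compared between arms only among Veterans who report a decision, a group formed after randomisation, so a difference may partly reflect selection

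*Protocol article*

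**What the plan says.** Under Aims and primary hypotheses, the secondary hypotheses for PREPARE versus control include "Veteran engagement and satisfaction with decision-making". Under Measures related to engagement and satisfaction in decision-making, the satisfaction part is given one instrument and one restriction: "Satisfaction with decision-making is assessed with the Decisional Conflict scale for those who report a decision was made". In Table 2 the row for the "Decisional Conflict Scale" (20 items) is marked at 1 week, 3 months and 6 months and has no baseline mark.

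Three places connect the intervention with deciding:

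- Background describes videos that show "how to make ACP decisions and to communicate with surrogates and clinicians".
- Background also states that "important secondary outcomes include identifying goals for medical care, communicating with surrogates and clinicians, and making informed medical decisions".
- The section on Veteran activation counts among active behaviours that patients "express concerns, offer opinions, state preferences, introduce new topics, or make decisions", and greater activation under PREPARE is itself a secondary hypothesis.

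The RCT efficacy analysis section describes mixed effects models for outcomes in general. It does not mention this scale or Veterans who report no decision.

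**The concern.** Randomisation makes the two arms comparable as randomised. It does not make subsets comparable when they are formed later by something the intervention may influence. Whether a Veteran reports a decision is settled after randomisation, and it can differ from visit to visit. If PREPARE changes how many Veterans report a decision, or which ones, the scored groups can differ in temperament, illness or readiness before any effect on satisfaction is considered.

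At stake is the reading of one secondary hypothesis. The article calls its secondary outcomes as clinically meaningful as the primary one. If hesitant Veterans are the ones drawn into deciding, a helpful intervention could appear to raise conflict. If confident ones are drawn in, an inert intervention could appear to lower it. The mixed model does not resolve this by itself: Veterans without a decision are not ordinary missing values, because they have no decision to rate. The scale also has no baseline score against which to check or adjust.

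**Working it through.** **1. The plan's own figures.** No power is stated for this scale. The primary outcome section gives 92% power for 15% versus 30%, and 80% for 15% versus 27%, with 175 per arm and a "two-tailed alpha of 0.05". A normal approximation with pooled variance under the null gives:

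- 15% v 30%: [0.15 − 1.96 × √(2 × 0.225 × 0.775/175)] / √((0.1275 + 0.21)/175) = 1.42, power 0.923.
- 15% v 27%: the same formula gives power 0.790.

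Both reproduce. They assume 175 analysable Veterans per arm, which does not carry over to an outcome scored only in deciders.

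**2. What has to be assumed.** The article gives no rate of reported decisions, no mean or SD for the scale, and no link between conflict and reporting a decision. Everything below is therefore illustration. The 15% and 30% are borrowed from the took-action rates in the secondary outcomes section. The other rates and the correlations are assumed.

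**3. Direction is not fixed.** Suppose 30% of controls and 45% of PREPARE Veterans report a decision. Suppose also that PREPARE has no effect on the score in the 30% who would decide anyway (mean 25 on an assumed 0–100 scale), and that the extra 15% score 35 or 15.

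- (0.30 × 25 + 0.15 × 35)/0.45 = 28.3, a difference of +3.3 from controls.
- (0.30 × 25 + 0.15 × 15)/0.45 = 21.7, a difference of −3.3.

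The sign depends wholly on who the extra deciders are.

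**4. Size under a normal selection model.** The treatment effect on the score is zero. The score (SD 1) has correlation ρ with a latent tendency to report a decision, and only the reporting rate p differs by arm. With c the (1 − p) normal quantile and λ(p) = φ(c)/p:

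- bias b = ρ × [λ(p1) − λ(p0)]
- variance v(p) = 1 − ρ² λ(λ − c)
- SE = √(v0/n0 + v1/n1), with n = 175p
- type I error = Φ(−1.96 − b/SE) + 1 − Φ(1.96 − b/SE)

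Example, 15% v 30% with ρ = 0.4: λ = 1.554 and 1.159, so b = 0.4 × (−0.395) = −0.158. Then v = 0.871 and 0.882, SE = √(0.871/26.25 + 0.882/52.5) = 0.224, b/SE = −0.71, and the type I error is 0.109.

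| Reporting a decision | Scored per arm | Bias, ρ 0.2 / 0.4 (SD) | Type I error, ρ 0.2 / 0.4 |
|---|---|---|---|
| 15% v 30% | 26 v 53 | 0.08 / 0.16 | 6.3% / 10.9% |
| 30% v 45% | 53 v 79 | 0.06 / 0.11 | 6.2% / 10.2% |
| 50% v 65% | 88 v 114 | 0.05 / 0.09 | 6.2% / 10.4% |

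Bias is shown in absolute size and reverses with the sign of ρ. It is zero when ρ = 0, and also when reporting rates are equal and selection works alike in both arms.

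**5. Precision.** The difference detectable at 80% power is 2.80 × √(1/n0 + 1/n1). This is 0.67 SD at 26 v 53, 0.50 SD at 53 v 79 and 0.40 SD at 88 v 114, against 2.80 × √(2/175) = 0.30 SD if all 350 were scored.

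**The case against.** The restriction is sensible measurement: the scale rates conflict about a decision, so a Veteran who made none has nothing to rate. The outcome is one of many in Table 2, is not listed in the Secondary outcomes section, carries no power claim and leaves the primary outcome untouched. The illustrated bias is also small beside the differences detectable in the same subsets. All of this stands and limits the weight of the point, but it does not turn the comparison among deciders into a randomised one.

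Some stronger readings are tempting and go beyond the text:

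- A reader might infer that PREPARE is expected to enlarge the group of deciders. No section predicts this. The phrase "communicating with surrogates and clinicians, and making informed medical decisions" can be read as being about the quality of decisions, and the activation section lists making decisions only as one kind of utterance in a recorded visit. If decisions are mainly prompted by illness, randomisation largely balances how often they arise.
- A reader might conclude that the groups are in fact non-comparable. That is a risk, not something shown.
- A reader might think that the missing baseline score rules out adjustment. Table 2 collects baseline readiness, self-efficacy, barriers and desired role in decision-making, which allow partial adjustment, though they cannot be relied on to remove the selection.
- A reader might take it as stated that the Decisional Conflict scores enter the general mixed model. The analysis section speaks of outcomes generically, and sensitivity analyses may be in an analysis plan that is not shown. Such a plan could redefine the question or add sensitivity analyses. It could not restore a comparison of everyone randomised on a score that non-deciders do not have.

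**Conclusion.** The point holds as a limit on inference. A between-arm hypothesis is tied to a measure taken only in a group formed after randomisation, with no baseline score, under an intervention that may affect entry to that group. A difference in the score may therefore partly reflect selection.

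The article does not allow size or direction to be determined. Under the assumed reporting rates and correlations of 0.2 to 0.4, a null effect would show as about 0.05 to 0.16 SD, with a type I error of about 6% to 11%. If reporting is unrelated to conflict there is no bias. The conclusion does not need PREPARE to produce more deciders; a change in which Veterans report a decision would be enough. One secondary hypothesis is affected. The correction is worth making because it is cheap and changes what may be concluded.

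**What to change.** 1. Report and compare, by arm and at each visit, the proportion reporting a decision, with all randomised Veterans as the denominator.
2. Label the Decisional Conflict score among deciders as a conditional, non-randomised comparison, and state that it cannot alone support the satisfaction hypothesis.
3. Accompany it with adjustment for baseline predictors already collected (readiness, self-efficacy, desired role, barriers) and a principal-stratum or bounding sensitivity analysis.

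A composite of having made a decision and scoring low on conflict, with no decision counted as failure, is defined for everyone and may look like the natural replacement. It should not become the test of satisfaction. With 30% versus 45% deciding and an assumed 60% of deciders in both arms below the cut-off, it gives 0.30 × 0.60 = 18% versus 0.45 × 0.60 = 27%. That is an apparent benefit from decision frequency alone. If only 40% of the extra deciders fall below the cut-off, PREPARE still leads: 0.18 + 0.15 × 0.40 = 24% versus 18%. It also needs a cut-off that the article does not supply.

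Cost: no new data, since the report of a decision already determines who is scored. The satisfaction hypothesis loses confirmatory weight, and a little analysis work is added.

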#### Measures related to surrogate decision maker reports of Veteran engagement

Because the preparation guide is highly focused on communication with one’s surrogate, it is important to measure whether Veterans engage in preparation behaviors with his/her potential surrogate for important corroborating information. We ask yes/no questions for all 5 preparation domains (Table 2, surrogate reports of patient engagement in ACP and other surrogate items). Surrogates are also asked about their knowledge of the Veteran’s wishes and confidence in making decisions on the Veteran’s behalf on a 5-point Likert scale with response options from “not at all” to “extremely”.

#### Measures related to acceptability and usability of PREPARE versus control

Acceptability and usability of PREPARE compared to an advance directive alone are measured with validated scales from our prior work according to the following: (a) ease of use and understanding (8-item scale), (b) personal usefulness in treatment decisions and discussions (6-item scale), and (c) attitudes about norms or expectations (6-item scale) [12]. We also assess how comfortable the Veterans are in completing the forms and the website, how helpful they find the materials, and how likely they are to recommend the materials to others [32]. These outcomes are important to measure to ensure PREPARE will be used in clinical practice and in the community.

#### Measures related to Veteran activation within primary care encounters

Veteran activation within the clinical encounter is assessed by audio-recording primary care visits using [name] communication coding system. This system defines activation as the degree to which patients ask questions, express concerns, offer opinions, state preferences, introduce new topics, or make decisions [33]. These behaviors are considered active because they have been shown to influence clinician’s behavior and treatment decisions [19]. We are interested both in activation in general throughout the consultation and in any discussions of ACP [34]. Therefore, we will assess overall activation and ACP-specific activation. The number of activation utterances will be assessed by independent, blinded coders and will be included in a composite measure. Utterances will also be coded as “self-initiated” or “prompted”, depending on whether the activation was solicited or encouraged by the physician. An increase of one patient activation utterance is considered clinically relevant. The codes of patient activation will be transformed into quantitative data and stored in a relational database that can be exported for quantitative analysis. To protect against rater drift and decay, continuous monitoring of inter-rater reliability will occur throughout the entire coding period by double-coding 20 % of the conversations. The coders will resolve any coding disagreements by conference; the entire team will resolve persistent disagreements.

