### Setting

The study is a randomized controlled trial with blinded outcome ascertainment conducted at the San Francisco Veterans Administration Medical Center (SFVAMC).

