### Intervention and control conditions

After the baseline interview, participants in the PREPARE arm review the PREPARE website (www.prepareforyourcare.org) in the research offices. Research staff are available to answer questions, but participants are asked to go through the PREPARE website (Steps 1 through 5) on their own and in its entirety. As participants progress through the website, PREPARE asks questions about overall life values and goals for medical care. At the end of the program, the participant is asked to make an action plan to do one ACP task in the next weeks to months. At the end of the interview, research staff print out the action plan and a summary of the Veteran’s medical wishes and compile this into a folder that also contains the PREPARE pamphlet, booklet, DVD, and the log-in code to the website. The PREPARE DVD contains the same information found on the website, but without interactive or tailored functionality. PREPARE arm participants are also given an easy-to-read advance directive to review and take home (http://www.iha4health.org/our-services/advance-directive/) [13]. Participants in the control arm are only given the advance directive, are asked to review it for at least 10 minutes and to take it home. The control arm is not given any information about the PREPARE materials. One to 3 days before the Veteran’s next scheduled primary care appointment, research staff call the PREPARE arm participants to remind them to bring in their action plan, summary of wishes and advance directive to their doctor’s appointment. For the control arm, research staff members only remind Veterans about their upcoming primary care appointment.

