### Blinding

Participants are blinded to group assignment. They are told that the purpose of the study is to help patients make difficult medical decisions, and that each participant would review one of two guides. This blinding is enhanced by each group obtaining some form of ACP materials, such as the easy-to-read advance directive. To ensure blinding of research staff for all follow-up outcome assessments, staff who had completed the baseline interview and randomization for a given participant will not conduct any follow-up interviews with that participant.

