#### Measures related to clinician responsiveness within primary care encounters

Clinician’s responsiveness within the clinical encounter will be assessed by rating “informativeness”, participatory decision-making, and partnership building. Overall informativeness will be rated on a 5-point Likert scale by two independent raters from recordings using [name] previously validated measure based on whether the clinician fully discusses what is causing the patient’s problem, the clinician explains everything to the patient, the clinician is very informative about the patient’s health, and the clinician’s recommendations are clear and easy to understand (score 4 to 20) [34, 35]. ACP-specific informativeness is adapted from this measure and uses the following three items: the clinician thoroughly explained everything about the ACP topic discussed, the clinician was very informative about ACP, and the clinician’s explanations about ACP are very clear (score 3 to 15). Clinician’s participatory decision-making/partnership building is adapted from Kaplan by [name] [34, 35]. For this measure, independent raters will decide on a 1 to 10 scale (1 = not at all and 10 = a great deal) whether the clinician involved the Veteran in the decisions, gave the Veteran a sense of control over medical care, and asked the Veteran to take some responsibility for ACP or medical care (scores 3 to 30).

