
#### Quantitative assessment of patient activation within clinical encounters

Differences in the number of patient activation utterances, ACP topics discussed, and length of time discussed will be compared between groups using mixed effects models as above with a random intercept for physician. Clinician race/ethnicity, and gender will be included as covariates as these variables are associated with doctor-patient communication [41]. We will also obtain the number of utterances that may signify clinician contamination (knowledge of study arm) to control for these findings.

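### The audio coders are described as blinded, but nothing in the design protects that blinding against arm-revealing talk on the recordings or in adjudication

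*Protocol article*

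**What the plan says.** All references are to the protocol article.

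- **Trial-level claim.** Under Setting: "The study is a randomized controlled trial with blinded outcome ascertainment". The Methods/Design part of the abstract makes a similar claim.
- **Activation coding** (Measures related to Veteran activation within primary care encounters): "The number of activation utterances will be assessed by independent, blinded coders and will be included in a composite measure". Coders also classify utterances as self-initiated or prompted, and ACP-specific activation is assessed as well as overall activation. One additional utterance is called clinically relevant. Twenty percent of conversations are double-coded. Disagreements are settled by the coders conferring and, if they persist, by the whole team.
- **Responsiveness ratings** (Measures related to clinician responsiveness within primary care encounters): "Overall informativeness will be rated on a 5-point Likert scale by two independent raters from recordings". Further items are rated from 1 to 10. This section calls the raters independent and does not use the word blinded.
- **Reminder calls** (Intervention and control conditions), 1 to 3 days before the visit. In the PREPARE arm, staff call Veterans to "remind them to bring in their action plan, summary of wishes and advance directive". In the other arm: "For the control arm, research staff members only remind Veterans about their upcoming primary care appointment".
- **Contamination count** (Quantitative assessment of patient activation within clinical encounters): "We will also obtain the number of utterances that may signify clinician contamination (knowledge of study arm) to control for these findings".
- **Blinding safeguard** (Blinding): "staff who had completed the baseline interview and randomization for a given participant will not conduct any follow-up interviews with that participant". No safeguard for recordings or coders is described there.

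**The concern.** A coder can be kept from the allocation list and still learn the arm from the recording. Here the intervention prompts one arm to bring arm-specific printouts into the room where the recording is made, and the analysis plan anticipates speech that may show knowledge of the arm. The only blinding procedure described concerns follow-up interviewers, who do not code the audio.

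The scoring needs judgement: what counts as activation, whether it is ACP-specific, whether it was prompted, and how informative or participatory the clinician was. Expectation can enter each of these. Cues are likeliest in ACP talk, which is where the ACP-specific outcomes are scored. Double-coding monitors agreement and drift; it does not detect a bias that both coders take from the same cue. Sending disagreements to the whole team opens a second route, because staff who ran the baseline session know the arm.

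Activation and responsiveness are named secondary hypotheses, and the article regards its secondary outcomes as no less clinically meaningful than the primary. An arm difference in them would be presented as a blinded finding.

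**Working it through.** **Step 1: the passages side by side.** The article gives no figure for coder blinding, so there is nothing to reproduce. The check starts from the text.

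| Question | What the article fixes |
|---|---|
| Are activation coders said to be blinded? | Yes, explicitly |
| Are responsiveness raters said to be blinded? | Only through the trial-level statements |
| Which visit is recorded? | The primary care visit (Discussion) |
| Who is asked to bring what to that visit? | PREPARE: action plan, summary of wishes, advance directive. Control: nothing |
| Which of these items reveal the arm? | Action plan and summary, produced only in PREPARE. The advance directive goes to both arms |
| Is arm-revealing speech anticipated? | Yes, as possible signs of the clinician's knowledge of arm |
| Who counts that speech, and when? | Not stated |
| What does the stated safeguard cover? | Follow-up interviewers |
| Who settles persistent disagreements? | The entire team, with no exclusion |

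Whoever counts the contamination utterances, the outcome coder must listen to the visit to score it and so hears any cue.

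**Step 2: possible size of the shift.** The documents do not give the share of recordings that reveal the arm, nor how a coder would react. Assume that a coder who recognises the arm credits s = 1 or 2 extra utterances in a share f of PREPARE recordings. Mean shift b = f × s:

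| f | s = 1 | s = 2 |
|---|---|---|
| 10% | 0.1 | 0.2 |
| 25% | 0.25 | 0.5 |
| 50% | 0.5 | 1.0 |
| 100% | 1.0 | 2.0 |

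The stated relevant difference is 1 utterance.

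**Step 3: false-positive probability with no true effect.** Inputs: 100 recordings per arm (the target under Secondary outcomes); SD of the utterance count assumed to be 3 to 6, because the documents give none. A simple two-sample normal approximation is used:

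z = b / (SD × √(2/100)); P(p < 0.05) = Φ(z − 1.96) + Φ(−z − 1.96).

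Example: b = 1, SD = 3 gives z = 1 / (3 × 0.1414) = 2.357, so P = Φ(0.397) + Φ(−4.317) ≈ 65%.

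| b | SD 3 | SD 4 | SD 5 | SD 6 |
|---|---|---|---|---|
| 0.1 | 6% | 5% | 5% | 5% |
| 0.25 | 9% | 7% | 6% | 6% |
| 0.5 | 22% | 14% | 11% | 9% |
| 1.0 | 65% | 42% | 29% | 22% |

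At shifts of 0.1 to 0.25 the error rate stays near its nominal 5%. At a shift of 1 it is four to thirteen times nominal. Nothing in the plan shows which row applies.

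**The case against.** **A tempting stronger reading** is that the activation and responsiveness scores are simply not blinded, contrary to what is claimed. The documents do not support that. Coders can be masked to allocation records, no passage says otherwise, and not every Veteran will mention the printouts. The contamination sentence concerns what the clinician knows. It says only that utterances may signify this, and it does not assign the count to the outcome coders. The responsiveness section never calls its raters blinded. Of the three items PREPARE Veterans are asked to bring, the advance directive is held by both arms. All of this stands, and it limits the point to blinding that is asserted but unprotected.

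**A journal article leaves coding logistics to a manual.** This is fair for the order of passes and the assignment of coders, and their absence alone would be no finding. But the article states a property, coder blinding, and also describes features that work against it: the one-sided reminder, the expected arm-related speech and the open adjudication. That tension lies in the text.

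**The alarming figures are one corner of a range.** This stands. The 65% needs an average of one extra utterance per PREPARE visit and an SD of 3, both assumed. At shifts of 0.1 to 0.25 the result is about 5% to 9%.

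**Masking the audio would do harm.** This also stands. Activation includes introducing topics and stating preferences, so mentioning an action plan may itself be an activation utterance. Masking it would remove outcome events mainly in one arm. Masking is therefore not recommended.

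**Conclusion.** The point holds in limited form. The article claims blinded activation coding and blinded outcome assessment overall, but the design does not protect either for the audio outcomes. Blinding may fail in an unknown share of recordings, more often in PREPARE and mostly in ACP talk. Under the assumed shares and reactions, the bias runs from 0.1 to 2.0 utterances: negligible at one end, and equal to or above the one-utterance relevant difference at the other. The plan includes no measurement that would tell which.

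This rests on two inferences: that coders hear the unedited visit, and that some Veterans or clinicians refer aloud to PREPARE-only materials. Both are reasonable, but neither is stated. The shifts and SDs are illustrations, not estimates.

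The scope is secondary outcomes in a target subset of 200 recordings. The primary outcome, documentation in the medical record, is not touched. The coding is described in the future tense, so the change still appears possible.

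**What to change.** Leave the audio unmasked and make four changes.

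1. **Restate the claim.** Describe activation coders and responsiveness raters as not told the allocation, rather than as fully blinded, and say that visit content may sometimes reveal the arm.
2. **Order the work.** Lock activation counts and responsiveness ratings for a visit before its contamination utterances are counted, and have someone who did not score that visit do the counting.
3. **Measure the problem.** Have each coder or rater record, for every visit, a guess of the arm and whether an arm-revealing cue was heard. Report both by arm, with a sensitivity analysis that takes account of them.
4. **Close the adjudication route.** Exclude staff who know a Veteran's allocation from resolving disagreements about that Veteran's recording.

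The cost is a change to the coding instructions and a little extra coder time on about 200 recordings, with no patient contact. One limit remains: cues are themselves a consequence of the intervention, so comparing or adjusting by cue status does not preserve the randomised comparison. The sensitivity analysis should be read with caution and should not replace the main result.
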